**Assessment of eligibility**			
Informed consent	X		
Inclusion and exclusion criteria	X		
Anamnesis	X		
**Assessment of safety**			
Physical examination	X	X	X
Vital signs	X	X	X
Assessment of adverse events		X	X
Previous and current medications	X	X	X
**Assessment of efficacy**			
Vital signs	X	X	X
Stridor	X	X	X
Taussig scale	X	X	X
Reintubation		X	X
**Other assessments**			
Other medications		X	X
**Deliveries of medication**			
Randomization and dispensing of the medication		X	X
Contact with the randomized-dispensing center	X	X	X

Visits 2 to 8, respectively: 15 min, 1 h, 2 h, 6 h, 12 h, 24 h, and 48 h after extubation

The timing of parameter recording is shown in Table 2.

**Table 2 Tab2:** Modified Taussig score

	Score			
	0	1	2	3
Clinical parameters				
Color	Normal	Normal	Normal	Cyanotic
Air entry	Normal	Mildly diminished	Moderately diminished	Substantially diminished
Retractions	None	Mild	Moderate	Severe
Level of consciousness	Normal	Restlessness if disturbed	Restlessness at rest	Lethargy
Stridor	None	Mild	Moderate	Severe (or no stridor if severe obstruction)

Upper airway obstruction is considered mild if score is less than 5 points, moderate-severe with at least 5 points. Modified Taussig score [13]

All interventions that patients require for their treatment are allowed but those that could affect the upper airway (respiratory tract infections, reintubations, etc.) will be recorded and will be taken into account in the statistical analysis.

For each participating center, a co-investigator will be appointed to verify the correct adherence to the study protocol, checking in every 8-h shift to confirm that the medication is prescribed in the treatment and that it has been administered. This investigator will also be responsible for complete follow-up of every patient.

A monthly communication newsletter regarding recruitment activity will be sent by email to all researchers. In this newsletter, researchers will also be encouraged to continue recruiting.

### 2.7. Evaluation of safety

The occurrence of adverse events from inclusion to study completion will be recorded for all patients. All patients, including those who discontinue their participation in the study, will be monitored until hospital discharge. Severe adverse events during hospital stay will be reported to the study coordinator and promotor. If severe adverse events occur, follow-up will be performed until remission or until a diagnosis is made and its association with the study medication is established.

A severe adverse event is defined as any adverse event that the patient’s treating physician considers to require treatment on the basis of the characteristics and clinical status of the patient. Severe hyperglycemia is any glycemia greater than 200 mg/dL that persists for more than 6 h or physicians consider to require treatment on the basis of the clinical status of the patient (or both).

Any unused medication will be disposed of in accordance with the protocol established by the pharmacy unit in collaboration with the unit of environmental management of the coordinating center, in compliance with ISO 14.001. Upon study completion, any unused or partially used medication will be sent back to the coordinating center.

Sample size

The estimated incidence of moderate to severe UAO symptoms is approximately 33% [1–3]. We consider a clinically relevant result to be a 50% reduction in the incidence of moderate to severe UAO symptoms in the treatment group.

To calculate the minimum sample size, a two-sample two-proportion two-tiled comparison test was used, and arcsine was used for the approximation for proportions (Cohen’s method). To detect a 50% reduction of incidence (33% UAO symptoms proportion in the placebo group and 16% expected proportion in the treatment group; that is, Cohen’s h effect size = 0.4) with 80% statistical power and a 5% significance level, 110 subjects per arm will be needed. A follow-up loss rate of 10% has been estimated.

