### 2.4. Randomization and masking

Patients will be assigned to one of the two therapy groups on a 1:1 ratio by simple randomization using a randomization table on EPIDAT 3.1 (Epidat: software package for epidemiological data analysis. 2006. Consellería de Sanidade, Xunta de Galicia, España; Organización Panamericana de la Salud; Universidad CES, Colombia). The coordinating center will send a table for sequential randomization of patients. This table will contain the number of the medication that has been assigned to each patient. The treatment group will not be detailed in the randomization table. This table will include a number of a reserve medication for use in case of deterioration or loss or if the drug is rendered unusable. The pharmacy unit of the coordinating center will send treatment-arm assignments labeled and blinded as established in the randomization table for each center.

The labeling and blinding of medication kits will be performed by the pharmacy unit of the coordinating center, which will keep an open record of these kits and their composition. This record will be coded and stored by the coordinating center pharmacist responsible for the labeling and submission of samples.

If severe or unexpected adverse events related to the medication appear the principal investigator will require the appointed pharmacist to unblind the codes identifying the sample. The principal investigator will be informed so that timely action can be taken. The unblinding of any code will be recorded by the pharmacist responsible for sample blinding.

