### 2.9. Data processing and auditing

Data from each patient will be collected and anonymized by a study member in a data log. Each study center will send their data logs to the coordinating center. The principal investigator will enter data from data logs into a single database for all study patients. An interim analysis will be performed by an independent data monitoring committee composed of members of the Central Unit of Clinical Research Support and Clinical Trials (UCAICEC) of the Gregorio Marañón Research Institute. The study will be interrupted only if the incidence of UAO or of severe adverse events is significantly higher in the steroid treatment group as compared with the placebo group. The final analysis will be carried out when the sample size has been reached. The UCAICEC will be responsible for auditing the trial independently from investigators yearly.

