The steroid most widely used for the prevention of post-extubation complications is dexamethasone [4, 7]. For this reason, we selected this medication for our study. However, there is variability in the timing of steroid administration prior to extubation. The intervals used range from 1 h prior to extubation to 24 h [4, 7]. In several studies, the administration of dexamethasone started 12 h prior to extubation [5, 7–9]. We decided to start the prophylactic therapy 6–12 h before extubation. This way, it is not necessary to delay extubation until the prophylactic treatment has been completed. Delayed extubation in the final stage of mechanical ventilation withdrawal is associated with a higher risk for trauma in the upper airways as a result of tube displacement when the patient moves or secondary to a more frequent need of secretion aspiration.

It is important that the study sample be composed of the patients who are more likely to benefit from steroids, as their use involves certain side effects such as hyperglycemia, hypertension, infection, and digestive bleeding [4, 7].

The most significant limitation of this study is the high number of patients needed. The number of participating centers is not very high, and completion of the study is expected to take a long time. Indeed, as it occurs in other trials with critically ill children, the percentage of inclusion is expected to be low because of difficulties in recruiting critically ill children. Another limitation of this study is the occurrence of other factors with impact on post-extubation respiratory failure (neurologic, cardiac, or respiratory diseases), which may hinder the assessment of a UAO. Moreover, it may be difficult to distinguish adverse events related to steroids (hyperglycemia and digestive bleeding) from events related to the underlying disease and critical state of patients. The results of this study will contribute to the existing evidence on prophylaxis for post-extubation UAO.

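### A severe adverse event is defined only by perceived need for treatment, yet the term drives unblinding and the harm criterion, so an expected dexamethasone effect such as treated hyperglycaemia can count towards both

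*Protocol article*

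**What the plan says.** Five statements in the protocol article bear on this point.

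- **Definition (section 2.7).** A severe adverse event is any adverse event that the patient's "treating physician considers to require treatment on the basis of the characteristics and clinical status of the patient". Death, threat to life, longer stay and lasting harm are not mentioned.
- **Hyperglycaemia (section 2.7).** The next sentence adds: "Severe hyperglycemia is any glycemia greater than 200 mg/dL that persists for more than 6 h or physicians consider to require treatment".
- **Unblinding (section 2.4).** "If severe or unexpected adverse events related to the medication appear the principal investigator will require the appointed pharmacist to unblind the codes". The principal investigator is then informed, so that action can follow.
- **Interruption (section 2.9).** "The study will be interrupted only if the incidence of UAO or of severe adverse events is significantly higher in the steroid treatment group", compared with placebo.
- **Reporting (section 2.7).** "Severe adverse events during hospital stay will be reported to the study coordinator and promotor".

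The Discussion (section 3) says of steroids that "their use involves certain side effects such as hyperglycemia, hypertension, infection, and digestive bleeding". Section 2.9 also states: "The principal investigator will enter data from data logs into a single database".

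**The concern.** One term serves three purposes: reporting, code-breaking and the harm criterion. Its definition asks only whether a physician thinks treatment is needed. In intensive care many ordinary events meet that test, and an effect that the article itself expects from dexamethasone is expressly included.

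Two consequences follow if the rules are applied as written.

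1. **Blinding.** Severe and unexpected are joined by *or* in section 2.4, so an expected event qualifies for unblinding once it is severe and judged related to the medication. Treated hyperglycaemia can meet both conditions, and should do so more often on dexamethasone. Code-breaks could then differ by arm.
2. **Safety monitoring.** The harm comparison counts an expected, treatable effect alongside grave events. An excess of the former can satisfy the criterion by itself, and an excess of the latter can be hidden among many minor treated events.

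**Working it through.** **Step 1: the texts side by side**

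| Section | Use of the term | Does treated hyperglycaemia qualify? |
|---|---|---|
| 2.7 | Definition: physician considers treatment required | Yes, and it is named expressly |
| 2.4 | Unblinding: severe *or* unexpected, and medication-related | Yes, if judged related; it need not be unexpected |
| 2.9 | Interruption: significantly higher incidence on steroid | Yes, it adds to the count |
| 2.7 | Report to coordinator and promotor | Yes |
| 3 | Listed steroid side effect | An excess on dexamethasone is to be expected |

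No section adds a condition of gravity.

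**Step 2: chance that the harm comparison is significant**

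The article gives no severe-event rates and no interim sample size, so there is no plan figure to reproduce for this point. The inputs are:

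- test: two-sided at 5% (section 2.8), critical value 1.960, counting only an excess on steroid;
- n = 55 per arm: assumed, half of the 110 per arm in the sample size paragraph;
- p0 (placebo) and p1 (dexamethasone), the share of children with at least one severe event: assumed, over a wide range.

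With p̄ = (p0 + p1)/2, the normal approximation for the pooled Z-test is

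probability ≈ Φ{ [√n (p1 − p0) − 1.960 √(2p̄(1 − p̄))] / √(p0(1 − p0) + p1(1 − p1)) }.

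- 70% v 75%: (7.416 × 0.05 − 1.960 × 0.6315)/0.6305 = −1.375, Φ = 0.085.
- 10% v 20%: (7.416 × 0.10 − 1.960 × 0.505)/0.500 = −0.496, Φ = 0.31.
- 20% v 40%: (7.416 × 0.20 − 1.960 × 0.648)/0.632 = 0.337, Φ = 0.63.

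Summing the two binomial distributions exactly gives:

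| Placebo v dexamethasone (assumed) | Chance of a significant excess on steroid, 55 per arm |
|---|---|
| 70% v 75% | 8% |
| 10% v 15% | 12% |
| 5% v 10% | 16% |
| 60% v 70% | 20% |
| 70% v 80% | 23% |
| 10% v 20% | 31% |
| 5% v 15% | 42% |
| 15% v 30% | 48% |
| 10% v 25% | 56% |
| 20% v 40% | 64% |

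The rows with a high background rate matter. If the definition really takes in most intensive-care events, both arms start high and a given excess is harder to detect.

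**Step 3: number of code-breaks**

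This cannot be calculated. Section 2.4 counts only medication-related events, and the article gives neither a rate of such events nor the share of severe events that physicians would judge related. Only the direction can be stated: towards the arm in which a listed side effect occurs.

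**The case against.** The case for leaving the text alone has real force on several points.

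- **The interim analysis is over.** Section 2.9 plans one, and section 3.1 reports that it was done in April 2017, with recruitment continuing. This stands. The stopping consequence is now confined to any further harm review.
- **Meeting the criterion does not stop the trial.** A reader might infer that a significant excess halts it automatically. Section 2.9 says *only if*, which is a necessary condition, and an independent committee performs the analysis. Nor do probabilities at 110 per arm describe a stopping risk: that is the full target, at which the final analysis is due.
- **Low rates are plausible.** The Discussion does not expect four doses to cause significant adverse events, and section 2.6 says that blood is drawn only for clinical purposes, which limits how much hyperglycaemia is detected. This is why the result is shown as a range.
- **Few grave events escape.** A reader might infer that grave untreated events are missed. The test is whether treatment is *considered* required, not whether it is given, so most life-threatening events qualify. What remains is, for example, a sudden death. Section 2.7 also states: "The occurrence of adverse events from inclusion to study completion will be recorded for all patients". The weakness is that nothing is classified by gravity, not that many grave events are lost.
- **Bias in the primary endpoint is not shown.** A reader might infer it because the principal investigator is informed at a code-break and also enters the data. Section 2.9 says that a study member collects each patient's data in a log, from which the principal investigator works. Nothing says that this person scores stridor or the Taussig scale, or that bedside assessors learn the allocation. The overlap of roles is avoidable, but it does not demonstrate bias.
- **Expedited reporting is not in the text.** Section 2.7 gives no timeline.
- **The full protocol may say more.** The article condenses version V02, which may hold seriousness criteria. The point, however, concerns what the article does state: an operative definition with consequences attached to it.

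**Conclusion.** The concern holds as a defect of definition with limited, unquantified consequences. As written, an expected and treatable dexamethasone effect can lead to unblinding when judged medication-related, and it counts towards the harm criterion together with grave events. This follows from sections 2.4, 2.7, 2.9 and 3 alone.

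The numerical size rests on assumptions. At an assumed 55 per arm and a two-sided 5% test, the chance of a significant excess on steroid ranges from about 8% to 64% over the assumed rates. No single value in that range is supported by the article, and no count of code-breaks can be given.

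Since the planned interim analysis is done, what is still affected is unblinding, the classification and reporting of safety events, the final safety comparison and any further harm review.

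**What to change.** Reconcile sections 2.4, 2.7 and 2.9 so that each states which events count for its purpose.

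1. Define a *serious* adverse event by standard seriousness criteria (death, threat to life, prolonged hospital stay, lasting disability, otherwise medically important), separately from severity and from need for treatment. Use it for reporting and for the harm criterion.
2. Tabulate expected treated effects, such as hyperglycaemia, separately by arm.
3. Limit code-breaking to events that are serious, unexpected and suspected to be related, or to cases in which the patient's care needs the allocation.
4. Keep the allocation from whoever enters the trial data.

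The cost is protocol wording and re-coding of events already recorded. No added procedures for patients are involved.

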### 2.8. Statistics

Categorical variables will be expressed as frequencies and percentages. Normality of continuous data will be assessed by the Kolmogorov–Smirnov test. Continuous variables will be expressed as mean values and standard deviation or as median values and interquartile range.

To compare the primary endpoint of outcome between the group receiving dexamethasone and the group receiving placebo, Z-test statistics will be used. Per-protocol analysis will be performed. An intention-to-treat analysis will be performed to guarantee the effect of randomization.

The association between other categorical variables will be assessed by chi-squared test or Pearson’s coefficient or by Fisher’s exact test, as appropriate, based on the sample size. Continuous variables will be compared by Student’s *t* test or Mann–Whitney *U* test. In comparisons of values with respect to time, Student’s *t* test of repeated measures or Wilcoxon test will be performed, as appropriate. Additional subgroup analysis according to age and pathologies will be performed.

Bilateral statistical tests will be used at a 5% level of significance. Statistical analysis will be performed by using SPSS version 20 (SPSS Inc., Chicago, IL, USA).

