## 1. Background

Critically ill pediatric patients frequently require endotracheal intubation. Post-extubation upper airway obstruction (UAO) is a common complication that affects up to a third of patients who require endotracheal intubation [1–3].

Owing to the small diameter of their airways, laryngeal edema is more frequent and severe in children than in adults. Indeed, this type of edema in children affects the subglottal region more frequently than the glottal region [2, 4]. Signs of airway obstruction include stridor and respiratory distress, which require reintubation in 6–13% of patients [1–3].

Risk factors related to post-extubation UAO include underlying respiratory or neurological disease, prolonged intubation (more than 36–48 h), reintubation, a young age (≤24 months of age), or infant weight of less than 5 kg [1, 2].

The obstruction of the upper airway has significant effects on the evolution of the patient. This complication may increase morbidity and mortality, length of hospital stay, duration of mechanical ventilation, and health care–related costs, especially when the patient requires reintubation [1, 2, 5, 6].

Steroids are among the most widely used therapies for post-extubation UAO, as they have anti-inflammatory effects, thereby reducing the risk for laryngeal edema and airway obstruction. A range of steroids such as hydrocortisone, methylprednisolone, and dexamethasone have been used for the prevention and management of post-extubation UAO [4, 7]. Contradictory results have been obtained in studies assessing the effectiveness of steroids in preventing post-extubation UAO [5–10].

A recent meta-analysis [7] of studies in adult patients with or without UAO risk factors receiving different regimens of steroids showed that steroids reduce the incidence of upper airway complications and reintubation in high-risk patients.

Studies in pediatric patients are based on widely heterogeneous samples of patients and doses and timing of prophylactic therapy ranging from 1 h to 24 h prior to extubation [4, 7].

In studies on the use of dexamethasone in children, a variety of regimens have been used versus placebo. Some authors report a decrease in the incidence of stridor [5, 8], whereas two studies show a reduction in the incidence of reintubation [8, 9]. A study in neonates concluded that dexamethasone reduced the risk for reintubation [10]. In contrast, this benefit has not been proven in other studies in children [11] and neonates [12].

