## 2. Methods

### 2.1. Study design

This is a multicentric, prospective, double-blind, randomized, placebo-controlled, phase IV clinical trial. Five pediatric intensive care units of hospitals in Spain will participate in the study. The study protocol was developed in accordance with the Standard Protocol Items: Recommendations for Interventional Trials (SPIRIT) checklist (Additional file 1). In May 2010, the study was registered with the European Clinical Trials Register (number 2009–016596-30) under the name “Steroids in the prevention of upper airway postextubation complications in critically ill children”.

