## 3. Discussion

Post-extubation UAO is a common complication that affects up to a third of patients, causing stridor and respiratory distress that require reintubation in 6–13% of patients [1–3]. There is no conclusive evidence of the effectiveness of steroids in preventing post-extubation UAO in pediatric patients [4]. If steroids were proven to be effective, they would become the standard treatment for those patients. This would help reduce morbidity and mortality, the length of hospital stay, the duration of mechanical ventilation, and hospital costs [1, 2, 5, 6].

On the basis of the limited evidence currently available, we designed a multicentric, randomized, double-blind study. The primary endpoints are post-extubation UAO symptoms, as they reflect the effects of steroids adequately. Reintubation is the most severe consequence of extubation failure and is the factor with the most significant impact on prognosis [2, 4]. Yet, as the incidence of reintubation is low, the number of patients needed for detecting differences between treatment groups would be very high. In addition, the recruitment of pediatric patients of these characteristics, who are often critically ill, is challenging. Therefore, the reduction in the incidence of reintubation, together with the occurrence of adverse events, was established as a secondary objective.

Prolonged reintubation is one of the most significant risk factors for reintubation [1, 5]. Considering the evidence provided in the literature [1, 3, 4, 11], we decided to use intubation for more than 48 h as an inclusion criterion. We included other risk factors reported to be associated with UAO [1, 2], namely tube size and characteristics (cuffed or uncuffed), underlying respiratory diseases, and previous manipulation of the airway. We decided to exclude patients who have received corticosteroids within the previous seven days given that the biological half-life of dexamethasone is 36–54 h and the elimination is completed (94%) after 4 half-lives.

Steroids are used for the management of multiple diseases. Although they involve some risks, the administration of four doses of steroids for prophylaxis of the UAO after extubation is not expected to cause significant adverse events [4, 7, 11]. Therefore, the potential benefit of steroids would outbalance its associated risks.

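### The unadjusted primary Z-test leaves unused the baseline risk factors that the protocol names and records; it is valid, but gives up a probably modest gain in precision and protection against chance imbalance

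*Protocol article*

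**What the plan says.** Primary analysis (section 2.8): "To compare the primary endpoint of outcome between the group receiving dexamethasone and the group receiving placebo, Z-test statistics will be used". The general rule there is "Bilateral statistical tests will be used at a 5% level of significance". Age and diagnosis return in section 2.8 only as subgroup analyses.

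Allocation (section 2.4): "Patients will be assigned to one of the two therapy groups on a 1:1 ratio by simple randomization". The section also mentions assignments "as established in the randomization table for each center", but names no blocks and no strata by risk factor. Section 2.1 adds: "Five pediatric intensive care units of hospitals in Spain will participate in the study".

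Risk factors (section 1): "Risk factors related to post-extubation UAO include underlying respiratory or neurological disease, prolonged intubation"; the list goes on to reintubation, age of 24 months or less and low infant weight. The Discussion says "We included other risk factors reported to be associated with UAO", meaning tube size and type, respiratory disease and earlier manipulation of the airway.

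Section 2.6 collects age, weight, diagnostic group, tube details, tube replacement, endoscopies and duration of intubation. It also says that interventions and events affecting the upper airway, such as infections and reintubations, will be considered in the analysis, without a method. Those are not the baseline risk factors.

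**The concern.** Simple randomisation balances prognostic factors only on average. A separate list for each centre does not force balance within a centre unless it is blocked. With about 220 children, a visible imbalance in age or diagnosis can arise by chance, and an unadjusted comparison leaves it in the estimate.

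The protocol believes that these factors predict the outcome and pays to collect them, so using them in the primary comparison needs no further design effort. At stake are some precision in a trial that calls its required number of patients its main limitation, and an awkward discussion if the baseline table comes out uneven. Because the protocol itself names the primary test, this concerns a choice it has made and not a detail left to an analysis plan.

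**Working it through.** **1. The plan's own sample size.** Inputs from the sample size paragraph: 33% v 16%, h = 0.4, two-sided 5%, 80% power, 10% loss.

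- n = 2(1.960 + 0.842)² / 0.4² = 98.1, so 99 per arm.
- 99 / 0.90 = 110 per arm. The stated figure reproduces and already contains the loss.
- Power of a Z-test at 33% v 16% is 79.9% with 99 per arm and 83.9% with 110.

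**2. How often does chance imbalance arise?** Assumption: a binary factor with 40% prevalence.

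- SE of the difference in prevalence = √(0.4 × 0.6 × 2 / n).
- n = 110 per arm: SE = 0.0661, so P(difference ≥ 10 points) = 13%.
- n = 60 per arm: SE = 0.0894, so P = 26%. This is only for reference, since section 3.1 reports just over 120 recruited and the final analysis is planned at full size.
- By simulation of simple randomisation of 220 children, arm sizes differ by 20 or more in 20% of trials. In a centre with 44 children (220 / 5), the split is 60:40 or worse in 17%.

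**3. How much does such an imbalance move the result?** Overall risk = (33% + 16%) / 2 = 24.5%. A 10-point imbalance shifts the risk difference by 0.10 × (risk with the factor − risk without it).

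| Assumed odds ratio | Risk without / with factor | Shift |
|---|---|---|
| 1.5 | 21.5% / 29.1% | 0.8 points |
| 2.0 | 19.3% / 32.3% | 1.3 points |
| 2.7 | 17.1% / 35.7% | 1.9 points |

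The SE of the risk difference at 110 per arm is √[(0.33 × 0.67 + 0.16 × 0.84) / 110] = 5.7 points. The shift is thus between about one seventh and one third of an SE, against a target difference of 17 points.

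**4. What does adjustment gain?** Assumption: three independent binary factors with prevalence 50%, 40% and 20% and a common odds ratio; 198 evaluable children; 33% v 16%; 6,000 simulated trials per setting. The pooled Z-test is compared with a logistic model standardised to the marginal risk difference.

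| Odds ratio per factor | Power, Z-test | Power, adjusted | Gain (points) | Variance ratio, adjusted / unadjusted |
|---|---|---|---|---|
| 1 | 80.7% | 80.6% | −0.1 | 1.02 |
| 1.5 | 78.8% | 79.5% | 0.7 | 1.01 |
| 2 | 80.6% | 82.6% | 2.0 | 0.96 |
| 3 | 79.6% | 84.2% | 4.6 | 0.91 |
| 4 | 81.9% | 88.2% | 6.3 | 0.83 |

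The Monte Carlo SE of each power is about 0.5 points. Type I error was 4.6–5.3% for the Z-test and 5.0–5.4% for the adjusted analysis.

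**5. How many covariates can the data carry?** Expected events: 0.245 × 220 = 54 at full size, and 0.245 × 120 = 29 at the number so far reported. Arm, age, diagnosis and duration are four terms, or 54 / 4 = 13.5 events per term. Four centre terms make eight, or 54 / 8 = 6.7, and 29 / 8 = 3.7 at 120 children.

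**The case against.** The strongest reply is that nothing here is an error. The Z-test matches the two-proportion comparison behind the sample size and keeps its error rate, and chance imbalance is already part of its standard error. That stands: the point is about a better method, not an invalid one.

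A reader might infer that the named factors are strong and that their omission could distort the result. The documents do not support this. They speak of factors related to or associated with UAO and give no odds ratio. Working step 3 shows that even a 10-point imbalance moves the estimate by about 1 to 2 points.

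A reader might also infer that the precision comes free. It does not: at an odds ratio of 1.5 or less the variance ratio is about 1.

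Two of the factors are partly removed by eligibility, since every child is intubated for more than 48 h and earlier extubation failure is an exclusion. The documents claim no further risk gradient beyond 48 h, so duration is an optional covariate at most.

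Finally, an analysis plan that is not shown could add an adjusted analysis. As the protocol stands, however, the primary test is the unadjusted one.

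**Conclusion.** The point holds as a weakness in efficiency and robustness. The primary comparison ignores baseline risk factors that the protocol names and collects, after randomisation that does nothing to balance them. There is no bias, and the sample size is not disturbed.

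The likely gain is modest and depends on a prognostic strength that the documents do not give: close to nil at an odds ratio of 1.5 or less per factor, about 2 power points at 2, and about 5 at 3. In variance terms, an odds ratio of 3 is worth about 99 × (1 − 0.91) = 9 children per arm. These figures assume three independent factors of equal strength with the stated prevalences and no centre terms.

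**What to change.** Before unblinding, define the primary analysis as a logistic model with arm and a short prespecified covariate list: age, respiratory or neurological diagnostic group and, optionally, log duration of intubation. Report the standardised marginal risk difference with its 95% CI, and keep the unadjusted Z-test as a sensitivity analysis.

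Three limits should be written in:

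- **Duration.** Section 2.6 records it up to extubation, which falls after randomisation. It should be counted to randomisation or first dose, which needs those times from the records; otherwise leave it out.
- **Centre.** Do not add several centre terms with about 29 to 54 expected events.
- **Events after randomisation.** The infections and reintubations mentioned in section 2.6 should not enter the primary model when they occur after randomisation.

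The cost is a change of wording and slightly more analysis work. Age and diagnosis are already collected. The downside is little or no gain if the factors prove weak. The allocation method need not be reopened, as recruitment began in 2013.
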